### 8.1.2 Control Intervention (standard/routine/comparator treatment)

Patients in the control intervention will be on fully suppressive antiretroviral regimen.

The control intervention may include several options:

- 2 NRTIs + either 1 NNRTI, 1 boosted PI or 1 INSTI;
- NRTI-sparing triple ARV regimen (e.g. 1 NRTI + 1 NNRTI + 1 INSTI);
- Dual therapy with protease inhibitor (such as PI + NRTI or NNRTI or INSTI).

Within-class antiretroviral switch (such as switch from TDF to TAF) are accepted during the study period only for patients randomized in the continuing cART arm. Other antiretroviral switch are discouraged and sponsor agreement is needed before the switch.

The following regimens will be excluded:

- Two-drug combinations with: 1 NRTI + 1 NNRTI, 1 NRTI + 1 PI without RTV, 1 NRTI + RAL, 2 NRTIs, MVC + RAL (not recommended by European guidelines);
- Triple NRTIs combination (not recommended by European guidelines);
- Dual therapy with DTG other than PI-based dual regimen, such as DTG + NRTI, DTG + NNRTI (simplified regimen already);
- PI monotherapy (simplified regimen already).

Standard monitoring includes a standard 12-weekly routine immunological and safety blood monitoring, including CD4 cell count, lipids and glucose, creatine kinase, renal and hepatic function tests, at affiliated SHCS sites.

### 8.1.3 Packaging, Labelling and Supply (re-supply)

The commercial product of Dolutegravir (Tivicay®), Emtricitabine (Emtriva®) and other antiretroviral drugs will be administered in this study (without deviation, i.e. only commercial product will be administered). The ARV drugs will be distributed to the participants according to usual local practice at the study centers. Each study centre distributing ARV will be resupplied using the hospital's routine order system. The study drugs (Tivicay® and Emtriva® and cART drugs) will be labelled with the following information in the local language: Short title of the study, Protocol CCER number, patient ID number, name of sponsor-investigator and/or principal investigator. Additional information such as date of IMP/prescription distribution can be added at site's discretion.

### 8.1.4 Storage Conditions

The investigational product will be stored securely at the study centers distributing ARV with limited access and under the recommended storage conditions.

ARV drugs must be stored at maximum 30°C. Study centre distributing ARV will be equipped with a temperature monitoring system and document storage temperatures in the investigator site file.

Temperature deviations of >30°C must be reported to the sponsor-investigator.

## 8.2 Administration of experimental and control interventions

### 8.2.1 Experimental Intervention

Dolutegravir 50 mg and Emtricitabine 200 mg will be administered per os once daily as dual therapy for a duration of 48 weeks. Participants will be requested to take the IMPs at approximately the same time each day (+/- 1 hour) with or without food. Dolutegravir and emtricitabine will be dispensed from study site or local pharmacy according to site practice at each scheduled visit. Study drug dispensing and return information will be recorded on the CRFs and drug accountability logs.

At the end of the study, all patients will be offered the possibility to continue their treatment with either a standard ART regimen or DTG + FTC dual therapy. This will be decided at treating physician discretion after discussion with the patient and depending on the efficacy of the strategy during the

study period. Subsequent follow-up will be made at the discretion of the treating physicians.

Participants in the patient-centered monitoring arm will be asked to select at least one of the three different options:

- Venipuncture for blood analyses: decentralised venipuncture, i.e. at peripheral laboratory nearer to their home or place of work, or with general practitioner, versus at their affiliated SHCS site;
- Drug delivery: delivery of ARV drugs/prescription by mail or at chosen pharmacy versus at their affiliated SHCS site;
- Assessment and clinical interview: phone call with study nurse/physician versus fa-to-face at their affiliated SHCS site.

At the end of the study, patients will continue regular monitoring as per SHCS requirements.

### **8.2.2 Control Intervention**

Participants randomised in the continuing cART arm will continue to take their standard fully suppressive antiretroviral therapy as previously, once or twice daily according to their antiretroviral regimen, at approximately the same time (+/- 1 hour) with or without food. All recommended American and European regimens are administered per os.

Patients randomized in the standard monitoring arm will continue a standard 12-weekly routine immunological and safety blood monitoring, including CD4 cell count, creatine kinase, lipids and glucose, renal and hepatic function tests, at their affiliated SHCS sites.

## **8.3 Dose modifications**

The dose of emtricitabine must be adapted according to kidney function. The dose of 200 mg once a day is the dose for a creatinine clearance of  $\geq 50$  ml/min. As participants will be excluded if creatinine clearance is  $< 50$  ml/min, there is no need for dose modification at enrolment. However, if creatinine clearance decreases during the study period, dose modification of emtricitabine will be made according to European guidelines, i.e.

- 200 mg every 48 hours if creatinine clearance between 30 and 49 ml/min (calculation preferably according to the CKD-EPI);
- 200 mg every 72 hours if creatinine clearance between 10 and 29 ml/min (calculation preferably according to the CKD-EPI);
- 200 mg every 96 hours creatinine clearance  $<10$  ml/min or haemodialysis (calculation preferably according to the CKD-EPI).

## **8.4 Compliance with study intervention**

Since non-adherence is one reason for simplified maintenance failure, special care will be given to optimize adherence. Patients known or suspected to be non-adherent will not be eligible for the study. All centres will apply standard specific interventions to promote patient adherence.

- Adherence will be documented at each visit, being face-to-face or through phone call, as participants will answer specific questions, identical to the questions used at the routine visits of the SHCS (86);
- Patients will be asked to fill in a diary with daily documentation of the date and time of drug intake, concomitant health conditions and medications at least in the case of any deviation from usual practice;
- Pill count will be performed at each visit, being face-to-face or through phone call.

Patient's adherence will be calculated as a percentage. Patients should have taken at least 80% of treatment pills during the study period to be considered in the per protocol analysis.

Patients with HIV-RNA  $\geq 100$  copies/ml at any time during the study will also benefit from DTG + FTC plasma concentration measurement.

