| Statistical Considerations: | 
DTG + FTC dual therapy is expected to be non- inferior to standard-of-care using a 12% non-inferiority margin assuming that 92% of patients are virologically suppressed at week 48 in the two comparison arms.
 
We will evaluate the proportion of patients with viral suppression at week 48 in each arm, and compute a Mantel-Haenszel risk difference (DTG+FTC minus cART) stratified by monitoring type with a two-sided 95% confidence interval. If the lower confidence limit is higher than -12% we will conclude non-inferiority. If the lower confidence limit is below -12% we will conclude that DTG + FTC is potentially inferior to cART. Per protocol (PP) and intention-to-treat (ITT) analyses will be performed. Exclusion criteria for PP will be: patients who discontinue treatment prematurely for reasons other than death, patients with a treatment adherence of less than 80%, or those who do not have HIV-1 RNA results available at week 48. For ITT analysis, all randomized patients will be analysed in the allocated group regardless of any protocol violations.
 |
| GCP Statement:              | 
This study will be conducted in compliance with the protocol, the current version of the Declaration of Helsinki, the ICH-GCP or ISO EN 14155 (as far as applicable) as well as all national legal and regulatory requirements.
                                                                                                                                                                                                                                                                                                                                                                                                                                                                                                                                                                                                                                                                                                                                                                                                                                                                          |

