## **11.4 Planned Analyses**

### **11.4.1 Datasets to be Analysed, Analysis Populations**

As recommended by the CONSORT statement (106), two analysis sets will be performed: per-protocol (PP) and intention-to-treat (ITT).

For PP analysis, we will exclude patients for the following reasons: patients who discontinue treatment prematurely (< 47 weeks), unless virological failure occurred before, patients with a treatment adherence of less than 80% while on treatment, those who do not have HIV-1 RNA results at week 48 (+/-21 days), unless virological failure occurred before, or patients with major protocol deviation(s) (i.e. any failure to obtain informed consent, violation of any inclusion criteria, not receiving the allocated treatment or monitoring). Per-protocol and intention-to-treat analyses should reach the same conclusion to consider DTG + FTC as non-inferior to standard treatment.

For ITT analysis, all randomized patients will be analysed in the allocated group regardless of any protocol violations.

All drop outs will be described and reasons for their discontinuation will be given where possible.

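### The per-protocol exclusions are written in three differing ways, and two of them can drop DTG + FTC virological failures from the set that must confirm non-inferiority

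*Protocol*

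**What the plan says.** Section 11.4.1 makes the claim depend on both analysis sets: "Per-protocol and intention-to-treat analyses should reach the same conclusion to consider DTG + FTC as non-inferior to standard treatment". Membership of the PP set is then described in three places.

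- **Section 8.4:** "Patients should have taken at least 80% of treatment pills during the study period to be considered in the per protocol analysis". There is no exception for virological failure.
- **Section 11.4.1:** excludes "patients with a treatment adherence of less than 80% while on treatment", also without an exception. The two exclusions on either side of it do carry one: "patients who discontinue treatment prematurely (< 47 weeks), unless virological failure occurred before" and "those who do not have HIV-1 RNA results at week 48 (+/-21 days), unless virological failure occurred before".
- **Synopsis, Statistical Considerations:** excludes "patients who discontinue treatment prematurely for reasons other than death" and also "patients with a treatment adherence of less than 80%, or those who do not have HIV-1 RNA results available at week 48". It names no adherence period and exempts failure nowhere.

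Sections 3.7 and 7.4 describe what follows confirmed failure, meaning two consecutive HIV-RNA values of at least 100 copies/ml. DTG + FTC patients stop study drug and move to standard cART before the genotype result. cART patients wait for that result, after which treatment in both arms is adjusted to it. Failing patients continue study procedures to week 48.

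**The concern.** A PP analysis supports a non-inferiority claim only if it can disagree with ITT for reasons other than the outcome. In the DTG + FTC arm, confirmed failure triggers the stop of study drug. If the stop, or the pills not taken after it, then removes the patient from PP, the outcome itself decides who is analysed. PP success rises and the difference between the arms shrinks.

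Section 11.4.1 appears written to prevent this, since it exempts failures in two of its exclusions. Section 8.4 and the synopsis can undo that exemption. The trial is open-label and Section 11.3 has HIV-RNA results with investigators within a week, so the choice between the versions could be made with outcomes already known.

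A second, smaller matter is that no version exempts failure from the adherence criterion itself, although Section 8.4 links the two: "Since non-adherence is one reason for simplified maintenance failure, special care will be given to optimize adherence".

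**Working it through.** **1. The plan's own figure.** Section 11.2 assumes 97% (cART) and 94% (DTG + FTC), a 12-point margin, one-sided 0.025 and 80% power. With unpooled variance:

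n = (1.960 + 0.842)² × (0.97×0.03 + 0.94×0.06) / (0.12 − 0.03)² = 7.85 × 0.0855 / 0.0081 = 82.9, so 83 per group, as stated. For 10% loss, 166/0.9 = 184.4, against 184 recruited. The sample size is not affected by this point.

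**2. Pills taken when DTG + FTC is stopped.** Inputs: visits at weeks 6, 12, 24, 36 and 48; a retest 2 weeks later (± 5 days, Section 6.1); visit windows of ± 7 days for weeks 6 to 36 (Section 9.3); 48 weeks of treatment; perfect adherence until the stop. The 80% threshold is 0.80 × 48 = 38.4 weeks. Share = (visit week + 2)/48.

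| Failure first seen | Nominal share | Range with windows |
|---|---|---|
| Week 6 | 8/48 = 16.7% | 13.1% to 20.2% |
| Week 12 | 14/48 = 29.2% | 25.6% to 32.7% |
| Week 24 | 26/48 = 54.2% | 50.6% to 57.7% |
| Week 36 | 38/48 = 79.2% | 75.6% to 82.7% |

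The week-36 limits are (35 + 9/7)/48 and (37 + 19/7)/48, so that case can fall on either side of 80%. A failure first seen at week 48 is confirmed nominally at week 50 and is unaffected.

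**3. What each version does with a perfectly adherent DTG + FTC failure who stops early.**

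| Version | Result |
|---|---|
| 8.4, allocated-regimen pills over 48 weeks | Leaves PP if first seen at weeks 6 to 24, usually at week 36 |
| 8.4, replacement cART pills also counted | Largely stays |
| Synopsis discontinuation rule | Leaves PP |
| 11.4.1 | Adherence to the stop is 100%; exempt from the discontinuation rule; stays |

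Under 11.4.1 the only failures removed by the adherence rule are those already under 80% before failing, in either arm.

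**4. Effect on PP.** Let r be the share of DTG + FTC failures removed. The documents give no value, so r is an assumption and its full range is shown. Expected PP success = p/(p + (1−p)(1−r)). For example, with p = 0.94 and r = 0.5: 0.94/0.97 = 96.9%, and the difference from 97% is −0.1 points. The last two columns come from a simulation on the margin (true 97% vs 85%, 92 per arm, 400,000 runs, unstratified Wald 95% interval).

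| r | PP difference at 97% vs 94% | PP alone passes on the margin | PP and ITT both pass |
|---|---|---|---|
| 0 | −3.0 | 3.9% | 3.9% |
| 0.25 | −1.6 | 17% | 3.9% |
| 0.50 | −0.1 | 53% | 3.9% |
| 0.75 | +1.4 | 94% | 3.9% |
| 1 | +3.0 | 100% | 3.9% |

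The 3.9% at r = 0, rather than 2.5%, reflects the Wald interval at rates near 1. The protocol cites a different Mantel-Haenszel interval.

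**The case against.** The strongest reply is that Section 11.4.1 is the section that defines the analysis sets. It measures adherence on treatment and exempts failures from two exclusions. Under it, stopping drug at failure removes nobody. Section 8.4 does not say that only pills of the allocated regimen count. Switched patients stay in follow-up with pill counts at each visit, and if their cART pills count, the imbalance largely disappears. All of this stands, and it is why the effect in step 2 is conditional.

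A reader might go further and infer that every DTG + FTC failure before week 48 is lost from PP while cART failures are untouched. The documents do not support that. The week-36 case straddles 80%. cART patients may also change regimen once the genotype is known. Some primary-outcome failures never reach the confirmed-failure stop: a single high value outside the blip rule (Section 5.1), or no data at weeks 36 and 48 (Section 11.5).

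It can also be said that excluding everyone under 80% adherence, suppressed or not, is ordinary PP practice, and that a blanket exemption for non-adherent failures would itself be tied to the outcome. That is fair. Section 7.1 also excludes patients with known or suspected poor adherence in the last 24 weeks, so such failures may be few. The question of patients who were non-adherent before failing is therefore better handled as a sensitivity analysis.

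The reply does not remove the contradiction. Section 8.4 states its own condition for entering PP, and the synopsis states a discontinuation rule that 11.4.1 contradicts.

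**Conclusion.** The point holds as a contradiction between Section 8.4, Section 11.4.1 and the synopsis over who enters PP. Under 8.4 read as allocated-regimen pills over 48 weeks, or under the synopsis discontinuation rule, perfectly adherent DTG + FTC failures can be removed. That would cancel the exemption 11.4.1 grants, mainly in one arm. Under 11.4.1 as written there is no built-in imbalance.

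It is tempting to read the PP-alone pass rates as the trial's error rate. They are not. ITT analyses all randomised patients and must agree with PP, so in the simulation the joint rate stays at 3.9% for every r. The loss is that PP could no longer serve as an independent confirmation, which is the role 11.4.1 gives it. The size of that loss depends on r, which is assumed. The calculation also removes failures only, and ignores suppressed patients whom the same rule would exclude. The correction should be made, but the point does not overturn the design.

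**What to change.** Use one rule, worded identically in Section 8.4, Section 11.4.1 and the synopsis:

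- Adherence = pills taken / pills prescribed of the allocated regimen, from baseline to the earliest of virological failure, end of allocated treatment or week 48. The 80% threshold stays.
- State that pills not taken after virological failure do not count against adherence.
- Carry the exemption for prior virological failure into the synopsis, for both early discontinuation and a missing week-48 result.
- As a sensitivity analysis, report PP with and without failures whose adherence before failure was below 80%.

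The last item should be defined by adherence up to the date of failure. Simply adding the existing exemption wording to the adherence clause would leave unclear the status of a patient who misses doses first and rebounds later.

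The cost is a wording change in three places plus one extra analysis, using pill counts already collected at each visit. The small downside is that a few more failures stay in PP, which makes it slightly more conservative. No treatment rule changes.

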#### **8.4.1 Retention**

Participant retention will be promoted using different strategies:

- Participants will be reminded of the critical importance of drug intake during visits, either face-to-face or through phone call;
- SMS reminders will be sent to patients 1 day prior to each scheduled study visit where feasible;
- Efforts will be made to adjust the timing of the study visits to the schedule of the patient whilst respecting the protocol given visit windows.

### **8.5 Data Collection and Follow-up for withdrawn participants**

Participants who withdraw from the study will be asked to come in for a close-out visit (named study discontinuation visit) where all assessments planned at week 48 will be done.

### **8.6 Trial specific preventive measures**

Concomitant medication(s) will be reviewed at baseline, at each visit thereafter and in case HIV-RNA is measured  $\geq 100$  copies/ml. Patients receiving anti-epileptic drugs such as carbamazepine, oxcarbamazepine, phenytoin, phenobarbital, St John's wort, or receiving the antibiotics rifampicin will not be eligible for the study. The concomitant administration of these drugs with dolutegravir decreases the plasma concentration of dolutegravir, and thus increasing the risk of virological failure. Patients on anti-tuberculosis treatment may be eligible at completion of anti-TB drugs. The use of these drugs is part of the exclusion criteria to the study and will be recorded in the screening CRF.

Pregnant women or breastfeeding mothers will not be eligible for the study as triple antiretroviral therapy is standard of care for these conditions. Pregnancy and breastfeeding are part of the exclusion criteria and will be recorded in the CRF.

Women of child-bearing potential will be screened for pregnancy at the screening visit of the study. Those who are found to be pregnant will be excluded from study participation (i.e. screening failure) and referred to an appropriate medical service.

Women of child-bearing potential included into the trial will further undergo urine pregnancy test once every 6 months (i.e. at week 24 and 48 visits). Results of screening and follow-up urine pregnancy tests will be recorded in the study CRF.

Women who become pregnant or start breastfeeding after randomisation will be switched to standard triple cART not containing dolutegravir and will continue the study. They will continue to be monitored for the development of adverse events (AE) or serious adverse events (SAE), and for pregnancy outcome.

After May 23, 2018, women of child-bearing potential and on dolutegravir are quickly identified by Sponsor-investigator and Study Sites and these women are all informed about the safety signal concerning DTG use in early pregnancy and risk of neural tube defect in infants born to women using DTG in early pregnancy. As communicated on May 25, 2018 to the leading Ethics Committee and to the DSMB (see appendix n° 7 and n° 8 respectively), these women are all asked to sign an information sheet explaining this risk. In case of willingness of pregnancy, they are switched to DTG-free regimen, at study investigator's discretion. In case of non-willingness of a pregnancy, the use of an effective contraceptive method (oral, injectable, implantable contraceptive and intrauterine contraceptive device are considered effective contraceptive methods as well as condom in stable couple and sexual abstinence) is proposed, if not already used by the women. Women of child-bearing potential, on dolutegravir, without willingness of a pregnancy, and refusing to use an effective contraceptive method are proposed to change their ART to a DTG-free regimen. If any of the above procedure is not respected, the sponsor will decide to withdraw the concerned patient from the study.

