## **7.4 Criteria for withdrawal / discontinuation of participants**

Participants will be withdrawn from the trial if:

1. The subject withdraws consent; in this case the patient will continue the antiretroviral treatment with a standard-of-care treatment (cART) and will continue regular follow-up with his/her treating physician;
2. Clinical reasons believed to be life-threatening by the physician, even if not addressed in the toxicity management protocol;
3. Subject is judged by the investigator to be at significant risk of failing to comply with the provisions of the protocol so as to cause harm to self or seriously interfere with the validity of the study result.
4. Study routine procedure must be stopped due to safety concerns.

Withdrawn participants will not be replaced.

Participants in the DTG + FTC dual therapy maintenance arm will discontinue study drugs if (non exhaustive list):

- diagnosed with virological failure defined as plasma HIV-RNA  $\geq 100$  copies/ml on two consecutive occasions;
- become pregnant
- start breastfeeding;
- requiring to use prohibited concomitant medications such as carbamazepine, oxcarbamazepine, phenytoin, phenobarbital, rifampicin or St John's Wort;
- presenting serious adverse events that necessitate to stop dolutegravir and/or emtricitabine;
- reasons related to conceiving and DTG potentially safety issue.

They will still be included in the study, continue their antiretroviral treatment with a standard cART. They can be switched to their previous ARV regimen or to a different one according to the genotypic resistance testing, drug-drug interactions profile and/or clinical evolution, and will complete study procedures until week 48. If the new regimen still fulfills the eligibility criteria the subject can continue the study, otherwise the subject will be withdrawn from the trial. In case of a pregnancy the viral load measurement will be performed once per month accordingly to the EACS guidelines.

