#### **Antiretroviral treatment and monitoring after the end of the study period**

At week 48 or study discontinuation visit, all patients will be offered the possibility to continue their treatment with DTG + FTC dual therapy, or previous-to-study cART regimen, or current cART regimen, or another regimen. This will be decided at the end of study by treating physician in collaboration with the patient. We suggest planning a viral load follow-up 6 weeks after an ARV de-escalating switch or a switch to a different regimen from the previous-to-study cART.

At week 48 or study discontinuation visit, all patients will be offered the possibility to continue their follow-up as standard monitoring or with one or more options from the patient-centered monitoring, according to local possibilities.

The treating physician will schedule follow-up after the end of the study period in any case, from the following cases:

- AE, SAE, SUSAR still ongoing (see point 10.1.3);
- Pregnancy still ongoing (see point 10.1.2 and 10.1.3);
- HIV-RNA  $\geq 20$  cp/ml, for which the procedure described at point 3.6 applies.

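### Section 8.6 answers non-respect of the dolutegravir conception safeguards with study withdrawal, so follow-up stops and a suppressed woman withdrawn before week 36 counts as an ITT failure

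*Protocol*

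**What the plan says.** Section 8.6 of the Protocol covers women of child-bearing potential who are on dolutegravir, in either treatment arm, after 23 May 2018. They are informed of the risk and sign a sheet. Those wanting a pregnancy are switched off dolutegravir, and the others are offered effective contraception. Women "refusing to use an effective contraceptive method are proposed to change their ART to a DTG-free regimen". The paragraph closes: "If any of the above procedure is not respected, the sponsor will decide to withdraw the concerned patient from the study".

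Under section 8.5, withdrawn participants are asked to "come in for a close-out visit (named study discontinuation visit) where all assessments planned at week 48 will be done". No later HIV-RNA is scheduled for them.

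Neighbouring rules separate stopping the drug from leaving the study:

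- Section 7.4 lists, among the reasons for DTG + FTC participants to stop study drug, "reasons related to conceiving and DTG potentially safety issue". Of those who stop it says: "They will still be included in the study, continue their antiretroviral treatment with a standard cART". They complete procedures to week 48, provided that the new regimen meets the eligibility criteria.
- Section 8.6 itself switches women who become pregnant off dolutegravir and keeps them in the study. Section 10.1.2 agrees that pregnancy is no ground for withdrawal.

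Section 11.4.1 puts all randomised patients in the ITT set and requires ITT and per-protocol to agree. Section 11.5 carries a week-36 HIV-RNA forward if week 48 is missing, and scores a patient with neither as a failure.

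**The concern.** The safeguard is about a drug, but the sanction ends observation. Stopping dolutegravir and stopping follow-up are separate decisions, and the last sentence of 8.6 ties them together.

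Two things are at stake. First, the ITT outcome: a woman with suppressed virus may be scored as a virological failure because of a contraception rule. Everyone in the DTG + FTC arm starts on dolutegravir, but only part of the cART arm takes it, so such failures fall mainly on one side of the comparison. Second, safety follow-up: scheduled adverse-event and pregnancy assessments stop for a woman in the group that prompted the rule. The post-study visits are described for subjects who have concluded week 48.

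**Working it through.** **1. From withdrawal to ITT failure.** Take a woman withdrawn at week 24 with HIV-RNA below 50 copies/ml. Her close-out sample is the last one scheduled. Section 5.1 gives the week-48 outcome a window of ±21 days, and week 36 has ±7 days (9.3.5), so her value falls in neither. Nothing in 11.5 substitutes an early close-out value, so she is a failure. If she is withdrawn after a week-36 sample, that value is carried forward and there is no such harm.

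**2. Who could be affected.** The rule starts on 23 May 2018; 36 weeks (252 days) earlier is 13 September 2017. With even accrual from 1 May 2017 to 30 June 2018 (assumed; the synopsis gives only the months), 135/425 = 32% were already past week 36.

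- Women in the DTG + FTC arm at the 28% target of 7.1: 0.28 × 92 = 25.8
- Not yet past week 36: 25.8 × 0.68 = 17.6
- Of child-bearing potential, if that share is 30% to 70% (assumed): 5.3 to 12.3

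The number who would decline every route is not in the document.

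**3. The plan's own figure.** Inputs from 11.2: cART 97%, DTG + FTC 94%, margin 0.12, one-sided 0.025. With the unpooled normal approximation,

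power = Φ[(0.12 − (pC − pT)) / √(pC(1 − pC)/n + pT(1 − pT)/n) − 1.96].

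At n = 83: SE = √((0.0291 + 0.0564)/83) = 0.0321, 0.09/0.0321 = 2.80, power 80.1%. This matches the plan's 83 per group.

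**4. Effect of k forced failures in the DTG + FTC arm, n = 92.** Set pT = p × (92 − k)/92, where p is the planned DTG + FTC rate. One failure moves the observed rate by 1/92 = 1.09 points, or 0.94 × 1/92 = 1.02 points in expectation.

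| Scenario | k = 0 | k = 1 | k = 2 |
|---|---|---|---|
| 94% vs 97% (11.2), no other loss | 84% | 70% | 55% |
| 92% vs 92% (synopsis), no other loss | 85% | 76% | 66% |
| 94% vs 97%, both rates × 0.90 (10% loss scored as failure) | 44% | 37% | 30% |

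If one woman is lost in each arm, at 94% vs 97% with no other loss, power is 77%.

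**5. On the confidence limit.** Take 86/92 on DTG + FTC and 89/92 on cART. The difference is −3.3 points with SE √(0.9674 × 0.0326/92 + 0.9348 × 0.0652/92) = 0.0317, so the lower Wald limit is −9.5%. One forced failure gives −10.9%; two give −12.2%, past the margin.

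**6. If she is kept but off DTG + FTC.** The dilution is about (0.97 − 0.94)/92 = 0.03 point per woman, against about 1 point for a forced failure.

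**The case against.** - **The group may be empty.** Section 8.6 accepts condoms in a stable couple and abstinence as effective methods, switches women who want a pregnancy, and offers a switch to those who refuse contraception. Only a woman who declines all of this, or the information sheet, reaches the last sentence. This stands: k is an assumption and may be 0.
- **The power figures can overstate the loss.** They put every case in one arm. Section 11.2 already allows at least 10% loss, about 9 of 92 per arm, and a withdrawn woman may be one of those nine at little extra cost. This stands. The third row of the table also shows that the larger driver is the missing-equals-failure rule in 11.5.
- **The close-out value might count as week 48.** Section 9.3.7 covers week 48 and the discontinuation visit under one heading. That leaves some room, but the ±21-day window and the silence of 11.5 favour the reading used here.
- **The kept women are not the same.** Those retained under 7.4 and 8.6 accepted a switch or stopped the drug. This is true. It explains a different treatment decision, but gives no reason to stop measuring HIV-RNA.
- **Care continues outside the trial.** Participants are in the SHCS or under its doctors, and pregnancies ongoing at the discontinuation visit are followed to resolution (10.1.2, 10.1.3). So the safety loss is limited to events arising later.

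A reader might also infer that withdrawal prolongs dolutegravir exposure. The sentence does not say that the drug stops, the product is commercial (8.1.3), and section 13 states: "At week 48 or study discontinuation visit, all patients will be offered the possibility to continue their treatment with DTG + FTC dual therapy". But section 13 lists other regimens beside it and leaves the choice to the treating physician with the patient. The document does not show that a withdrawn woman would stay on dolutegravir.

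**Conclusion.** The point holds in a narrow form. The last sentence of 8.6 ends scheduled follow-up where stopping the drug would do, and with 11.5 it can turn a suppressed woman into an ITT failure if she is withdrawn before week 36. The cost is about 1 point of the 12-point margin for each woman affected. One woman in the DTG + FTC arm would lower power by 14 points (84% to 70%) at the 11.2 rates with no other loss, and by about 8 points (44.3% to 36.5%) on top of a 10% loss scored as failure. The cost is smaller still if she falls within that loss. How many women this concerns is unknown, probably very few and possibly none.

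Failures added to the DTG + FTC arm work against non-inferiority, so they cost power and do not inflate type I error. That direction rests on the cases falling mainly in that arm.

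A reader might take 8.6 to contradict 7.4. It does not: items 3 and 4 of 7.4 already permit withdrawal for non-compliance or safety. This is a poorly chosen consequence, worth changing because the change is cheap. By the planned dates the 48-week phase ended in May 2019, before version 5.1 of 30 July 2019, so under this version only post-study follow-up could still benefit.

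**What to change.** Replace the last sentence of 8.6 with wording such as:

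> Where this procedure is not followed, the sponsor will stop dolutegravir as study treatment and the investigator will recommend a DTG-free regimen. Unless she withdraws consent, the participant, whichever her arm, stays in follow-up with the planned HIV-RNA, adverse-event and pregnancy assessments to week 48, and may enter the post-study visits.

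It belongs in 8.6 because the retention rule in 7.4 covers only the DTG + FTC arm and depends on the new regimen being eligible.

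The costs are a few more scheduled visits, a dilution of about 0.03 point per woman from ITT outcomes observed off the allocated regimen, and a likely ethics notification or amendment. The change does not rescue the per-protocol set: a woman who stops DTG + FTC before week 47 without earlier virological failure is still excluded under 11.4.1.
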